### 8.2. Secondary Outcomes

To assess the effect of EVC on the neurobehavioral and developmental outcomes of newborns, as well as on maternal stress and presence in the NICU, the values for the different scales and questionnaires will be compared (at the time points specified in the Secondary Outcome Measures) between the intervention and control groups. Confounding variables will be entered in the analysis (i.e., familiar socio-economical score, gestational age at birth) to partial out any effect which they could have on the difference between the outcome measures. For continuous variables the Wilcoxon-Mann-Whitney test will be applied, while for categorical variables the chi-squared test (or Fisher’s exact test where appropriate) will be applied. 

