## 2. Hypothesis

We hypothesise that EVC can enrich the preterm infants’ sensory and interactional experience and that this mother-driven environmental enrichment impacts the infant’s physiology by enhancing cardiorespiratory maturation and autonomic regulation that persist during interventions and possibly heart rate variability (HRV). 

HRV is representative of the functional state of an infant’s autonomic nervous system (ANS). ANS maturation is accompanied by increasing HRV with a concomitant augmentation of parasympathetic activity. A preterm infant’s GA correlates with HRV; preterm infants demonstrate lower HRV parameters than term infants [57]. Early interventions aimed at involving parents in engaging with preterm infants have shown important effects on an infant’s HRV [58] and respiratory sinus arrhythmia [59], the two indices of autonomic regulation and maturation of the ANS. 

We also hypothesise that an interactive and relational-based enriched auditory environment can impact an infant’s neurobehavioral development, as evidenced by the General Movements score (for details, see Secondary Outcome Measures).

Specific interventions directed at improving early care in the NICU, such as the Newborn Developmental Care and Assessment Program [60], skin-to-skin care [61], and massage therapy [61,62], have shown significant effects on neurodevelopmental outcomes. Research suggests that early interventions aimed at reducing the sequelae of prematurity can have positive effects, especially in the short-term periods [63,64]. However, many interventions lack long-term assessments, particularly on the infants’ neural and behavioural development [65].

Thirdly, in a long-term prospective design, we will test if earlier and regular exposure to salient linguistic stimuli in interactive contexts will impact preterm infant development, particularly the cognitive and linguistic performance, at 6, 12, and 24 months CA. Adult language input is important for healthy language development and preterm infants are at risk for long-lasting language delays [66,67]. Thus, we expect to find a direct effect of the intervention on the aforementioned developmental domains.

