### 3.7. Sample Size and Power Analysis

The main outcome measures for the primary outcome will be the low-frequency (LF) and high-frequency (HF) power of the HRV measure. We expect the baseline measurement mean value (±standard deviation) of LF and HF power for preterm infants to be 31 ± 4.9 Hz and 15 ± 2.6 Hz, respectively [58]. We assume that the treatment in the experimental population is effective if the mean values of LF and HF power reach 25 ± 4.9 and 17 ± 2.4 Hz, respectively. 

With an alpha setting at 0.025 and beta setting at 0.80, it is necessary to enroll 29 patients per group. Assuming a 20% loss, we aim to enroll at least 80 patients total (40 per group).

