#### 5.2.1. Infant’s Measures

Neurobehaviourally, GMs [8] will be measured at T0 and T1 (at term equivalent age) in both groups. Infants will be reassessed at 3 months. The GMs quality from video recording will be scored according to the Ferrari optimality score [74]. Two blinded coders will attribute a single final score for each infant at each time point. Inter-rater reliability will be assessed, and the mean scores will be compared between the intervention and control groups at each time point.

Developmental Level: Developmentally, the Griffiths Mental Development Scales (GMDS) [75] and a routine neurological examination (EON) will be administered to infants by trained researchers at 6 (T2), 12 (T3), and 24 (T4) months CA. 

These GMDS assess infant development across five main areas (locomotor, personal and social skills, hearing and language, eye and hand coordination, and performance), providing a general developmental quotient (DQ) of infant’s abilities and five sub-scale quotients (SQ).

The EON will be assessed with a final positive or negative score. In case of a negative score, the infant will be excluded from further analyses. The Italian version of the MacArthur–Bates Communicative Development Inventory [76,77] will be completed by parents at 12 (Gestures and Words Form) and 24 (Words and Sentences Form) months CA. Furthermore, the expressive and receptive language test, Parole in Gioco [78], will be administered to infants by trained researchers at 24 months. Each child, at each time point, will receive a final score for each questionnaire, measured as a discrete numeric value. 

Next, an audiological evaluation using an auditory brain system response will be performed within 3 months of CA and repeated at 12 and 24 months with behavioural audiometry techniques. A positive or negative evaluation will be obtained. In the case of negative audiological evaluation, the infant will be excluded from analyses.

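### The Griffiths scores at 6, 12 and 24 months are compared visit by visit with a rank test that ignores each child's other visits and cannot take the covariates the plan says will be entered

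*Protocol article*

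**What the plan says.** Section 5.2.1 (Infant's Measures) says that the Griffiths scales "will be administered to infants by trained researchers at 6 (T2), 12 (T3), and 24 (T4) months CA", giving one general quotient and five sub-scale quotients at each visit.

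Section 8.2 (Secondary Outcomes) states that scale and questionnaire values "will be compared (at the time points specified in the Secondary Outcome Measures) between the intervention and control groups". On method it says: "For continuous variables the Wilcoxon-Mann-Whitney test will be applied". It also says: "Confounding variables will be entered in the analysis (i.e., familiar socio-economical score, gestational age at birth". It names no analysis that links a child's visits.

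Section 2 (Hypothesis) expects an effect on development, "particularly the cognitive and linguistic performance, at 6, 12, and 24 months CA".

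Section 3.7 gives the only attrition figure: "Assuming a 20% loss, we aim to enroll at least 80 patients total". That section sizes the trial on low- and high-frequency heart rate variability (HRV) power. It gives no sample size or power for the Griffiths scores.

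**The concern.** The Wilcoxon-Mann-Whitney test compares one score per child between two groups. Used at 24 months, it sees only the children who attended at 24 months. A child with Griffiths scores at 6 and 12 months who then leaves follow-up drops out of that comparison, although two correlated scores are on file.

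Two things are at stake. If leaving depends on how the child was doing, and differently in the two arms, the attenders are no longer comparable, and the scores that could correct for this go unused. Families know their arm (section 6), so such a pattern is possible. If leaving is unrelated to the score, nothing is biased but some precision is given up.

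There is also a conflict within section 8.2. It promises adjustment for socio-economic score and gestational age, but the only test it names for continuous outcomes has no place for a covariate.

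**Working it through.** **The plan's own figure.** Section 3.7 states: "With an alpha setting at 0.025 and beta setting at 0.80, it is necessary to enroll 29 patients per group". Reading the 0.80 as power and the alpha as two-sided, HF power with a difference of 17 − 15 = 2 and a variance of (2.6² + 2.4²)/2 = 6.26 gives n = 2 × (2.241 + 0.842)² × 6.26 / 2² = 29.8, so 30 per group. That is close to the stated 29. Allowing for 20% loss, 29/0.8 = 36.3, so 37 per group, below the planned 40. The figure reproduces, but it concerns HRV and says nothing about Griffiths follow-up.

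**Inputs for the Griffiths check.**
- From the plan: 40 per arm; visits at 6, 12 and 24 months.
- Assumed: 20% of each arm lost by 24 months, leaving 32; correlation between visits 0.3 to 0.8, either equal between all pairs of visits or decaying with visit separation (first-order autoregressive); scores in SD units. The article gives none of these for the Griffiths scores.

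**Precision at 24 months.** Suppose every loss falls between 12 and 24 months. A likelihood-based model gives the 24-month mean a variance of (1 − R²)/32 + R²/40 per arm, where R² is the share of the 24-month variance explained by the two earlier scores. Divided by the attenders-only value of 1/32, the ratio is 1 − 0.2R².

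With equal correlation r, R² = 2r²/(1 + r). With decaying correlation, R² = r².

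| r | Ratio, equal correlation | Ratio, decaying correlation |
|---|---|---|
| 0.3 | 0.97 | 0.98 |
| 0.5 | 0.93 | 0.95 |
| 0.7 | 0.88 | 0.90 |
| 0.8 | 0.86 | 0.87 |

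If losses are spread over follow-up (5%, 10% and 20% lost by the three visits), the ratio is 0.89 to 0.99. If all losses precede 6 months, the children lost have no earlier Griffiths score and the ratio is 1.00. The gain is therefore 0 to 14%.

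For scale, at an assumed constant effect of 0.65 SD and two-sided 0.05, power at 24 months is about 0.72 for the rank test and 0.74 to 0.80 for the model's 24-month contrast.

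**Bias at 24 months.** Assume no true effect. Let the log-odds of loss before 24 months be logit(0.2) + b × (12-month score) in one arm and logit(0.2) − b × (12-month score) in the other. Because loss depends only on the 12-month score, the mean 24-month score among attenders is r times their mean 12-month score. The two arms shift in opposite directions, so the bias in the mean difference is 2r × |mean 12-month score among attenders|.

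| b per SD | Expected loss | Mean 12-month shift among attenders | Bias, r = 0.5 | Bias, r = 0.7 |
|---|---|---|---|---|
| 0.25 | 20% | 0.050 | 0.05 SD | 0.07 SD |
| 0.5 | 21% | 0.101 | 0.10 SD | 0.14 SD |
| 1 | 24% | 0.204 | 0.20 SD | 0.29 SD |

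With 32 per arm the standard error of the difference is √(2/32) = 0.25 SD, so a bias of 0.05 to 0.14 SD is about 0.2 to 0.6 standard errors. If the dependence is in one arm only, the bias halves (0.10 to 0.14 SD at b = 1). If it is the same in both arms and there is no effect, the bias is zero. A repeated-measures likelihood model is essentially unbiased in all these scenarios, as expected, because loss was made to depend only on an observed score. The bias is worked out for means; the rank test uses the same attenders and shifts in the same direction.

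**The case against.** The strongest reply is that the plan does what it says it will do. The hypothesis reads naturally as performance at each of three ages, and section 8.2 compares at each age. These are secondary outcomes without a power claim, and a per-visit rank test is valid where loss is unrelated to outcome. All of that stands.

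Three stronger readings are tempting and are not supported:

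- *An overall developmental effect is being estimated inefficiently.* The article defines no such effect. An average over three visits does have a much smaller variance than a single visit (0.41 to 0.87 of the 24-month value under the assumptions above), but it is a different quantity. It could hide an absent effect at 24 months, and section 2 itself says that early interventions help mainly in the short term.
- *The 24-month result will be badly biased.* The largest figures need strong dependence of loss on the earlier score, in opposite directions by arm. Nothing in the article points to that. Section 6 also has the cognitive and linguistic tests administered and coded blind, although families know their arm.
- *The plan expects 20% loss at 24 months.* The 20% belongs to the HRV sample size, an in-hospital outcome. Using it for two-year follow-up is an assumption.

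It can also be said that the covariate sentence implies some model, with details and missing-data handling held in a document not shown. That may be so. But the article names a specific test and a visit-by-visit comparison, and that test cannot do what the covariate sentence promises. The conflict lies in the published text and is not an omission.

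**Conclusion.** The point holds as a moderate, inexpensive improvement to a secondary analysis. The named method discards Griffiths data already collected on children who leave later, and it cannot carry out the adjustment stated beside it.

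The case rests more on protection against arm-dependent loss, and on resolving that conflict, than on precision. The possible bias is about 0.05 to 0.14 SD under moderate opposite-direction dependence and 0.20 to 0.29 SD only under strong dependence, for a visit correlation of 0.5 to 0.7. The variance saved at 24 months is 0 to 14% and vanishes if losses come before 6 months. Correlation, loss rate, loss timing and loss mechanism are all assumed. A reader should not conclude that the per-visit tests are invalid in themselves.

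**What to change.** For the Griffiths general quotient and the five sub-quotients, make the main analysis a linear mixed model for repeated measures:

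- fixed effects for arm, visit, arm-by-visit, gestational age at birth and socio-economic score;
- unstructured within-child covariance;
- allowance for twin clustering, for example a family-level random effect, since section 3.8 randomises twins together;
- all available visits included.

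Report the arm difference with a 95% confidence interval at 6, 12 and 24 months. An average over visits may be added as a further estimand, but should not replace the 24-month contrast.

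Keep the per-visit Wilcoxon-Mann-Whitney tests as a supportive analysis, described as unadjusted and restricted to attenders. They differ from the model in missing-data handling and covariates as well as in distributional assumptions, so disagreement should not be read as a test of normality alone.

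The cost is a change to section 8.2 and some programming, with no new data. The downside is reliance on approximate normality and on loss being explained by observed data.

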### 3.8. Randomisation

A centralised patient randomisation will be performed using a secure, web-based randomisation system, through which the study investigator of each centre can register new patients and obtain the treatment arm assignment.

A block allocation sequence with variable block sizes (block size 2–4), stratified by GA and gender, will be generated using Stata statistical software (StataCorp, College Station, TX, USA) with the “ralloc” command. In case of twins, randomisation will be conducted at the level of the family (i.e., twins will be randomised to the same group). The allocation sequence will be concealed from the investigators.

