#### 4.1.2. Maternal Measures

Baseline demographic data will be collected from the digital recorded data for each patient. In addition, a socio-economic status questionnaire will be administered to each participant and the Socio Economical Score (SES) will be calculated. To determine baseline stress, the Parental Stressor Scale (PSS-NICU) questionnaire will be administered to the mothers before intervention (T0) and before discharge, both in the intervention and control groups. The PSS-NICU [71,72] aims at assessing the parental perception of stressors derived from the physical and psycho-social environment of the NICU across three domains: their parental role, their infant’s behaviour and appearance, and the sights and sounds in the NICU. For each domain, a mean score will be assessed, and a final composite stress score will be calculated from the mean values of the single scores. Each mother, at each time point, will receive a final score for the single questionnaire (range 0–10). 

A questionnaire on musical experience [73] will be administered at T0. The questionnaire gives three scores for musical expertise, musical habits in everyday life, and music as an emotional experience. 

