#### 5.2.2. Maternal Measures

##### Stress Measures

To determine stress, questionnaires administered at baseline will also be administered at hospital discharge. The final PSS-NICU scores will be compared between the intervention and control groups, and between two different time points (i.e., pre- and post-intervention).

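### Secondary outcomes: adjustment for socio-economic score and gestational age is promised, but the only tests named take no covariates

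*Protocol article*

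**What the plan says.** Section 8.2 (Secondary Outcomes) covers the neurobehavioural and developmental outcomes, maternal stress and maternal presence. For all of them, "the values for the different scales and questionnaires will be compared" between the two arms. It then commits to adjustment: "Confounding variables will be entered in the analysis (i.e., familiar socio-economical score, gestational age at birth) to partial out any effect". The next sentence assigns tests by type of variable: "For continuous variables the Wilcoxon-Mann-Whitney test will be applied, while for categorical variables the chi-squared test", or Fisher's ("exact test where appropriate) will be applied").

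Other sections bear on this:

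- Section 4.1.2 provides the socio-economic covariate: "a socio-economic status questionnaire will be administered to each participant and the Socio Economical Score (SES) will be calculated".
- Section 3.8 describes an allocation sequence "stratified by GA and gender, will be generated using Stata statistical software", and puts twins in the same arm.
- Section 5.2.1, on General Movements: "the mean scores will be compared between the intervention and control groups at each time point".
- The Stress Measures section, on PSS-NICU: "The final PSS-NICU scores will be compared between the intervention and control groups, and between two different time points".

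**The concern.** Two adjacent sentences in section 8.2 do not fit together. One says that covariates enter the analysis. The other specifies analyses that have no place for them. An analyst who follows the named tests reports unadjusted comparisons, while a reader of the protocol believes that gestational age and socio-economic score have been accounted for. An analyst who follows the adjustment sentence has to choose a model that the article does not name.

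The section governs every secondary outcome, so it carries the trial's neurobehavioural, developmental and maternal hypotheses. Two things are at stake. One is the precision that prognostic covariates could add in a small trial. The other is certainty, fixed before the data are seen, about which of two possible results is the main one.

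**Working it through.** **Step 1: can the named tests deliver the promised adjustment?**

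| Section 8.2 element | What it requires or allows |
|---|---|
| Adjustment for socio-economic score and gestational age at birth | An analysis with covariate terms |
| Wilcoxon-Mann-Whitney (continuous) | Two-group rank comparison, no covariate term |
| Chi-squared or Fisher's exact (categorical) | Contingency table, no covariate term |

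No regression, ANCOVA, rank ANCOVA, mixed model, van Elteren or Cochran-Mantel-Haenszel test is named anywhere in the article. Section 8.1 names Friedman and Kruskal-Wallis tests, which take no covariates either. Stratified relatives of the named tests exist, but they would need cut-points for both covariates, and the article gives none. The stated methods therefore do not produce the stated adjustment.

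**Step 2: what could adjustment be worth?** The plan gives no figure to reproduce here, so this is an illustration.

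Inputs:
- Per arm: 40 × (1 − 0.20) = 32, from the 40 per group and 20% loss in section 3.7.
- Standardised difference d = 0.6 and two-sided alpha 0.05: assumptions.
- Correlation r between the covariates jointly and the outcome: assumption, shown as a range.

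Formulas: covariates with correlation r reduce the residual SD by the factor √(1 − r²). The effective difference becomes d/√(1 − r²), and the equivalent sample-size multiplier is 1/(1 − r²). Power is from the noncentral t distribution with 32 per arm, ignoring the few degrees of freedom spent on covariates. For r = 0.5: 0.6/√0.75 = 0.693, and 1/0.75 = 1.33.

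| r | Effective d | Power | Equivalent to more infants |
|---|---|---|---|
| 0 (unadjusted) | 0.600 | 65.6% | none |
| 0.2 | 0.612 | 67.4% | 4% |
| 0.3 | 0.629 | 69.7% | 10% |
| 0.4 | 0.655 | 73.2% | 19% |
| 0.5 | 0.693 | 77.9% | 33% |
| 0.6 | 0.750 | 84.0% | 56% |

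**Step 3: check against the named test itself.** The first row is t-test power. A simulation with the same assumed n, d and alpha, and one covariate explaining 10%, 30% or 50% of the outcome variance, gave Wilcoxon-Mann-Whitney power of about 63% throughout. A linear model with the covariate gave about 70%, 80% and 91%. The rank test gains nothing from the covariate, however prognostic it is.

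**Step 4: which rows apply to which outcomes?** A T0 score is described only for General Movements and PSS-NICU. Griffiths, the MacArthur-Bates inventory, Parole in Gioco and maternal presence have none. For those, r must come from socio-economic score, gestational age and sex, within an eligible range of 25+0 to 32+6 weeks. The lower rows are the safer expectation there.

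**The case against.** The strongest reply is that this is a condensed article. Section 8.2 can be read as an adjusted analysis whose model is left to a fuller document, accompanied by simple group tests. It nowhere says that the named tests are the only analyses. That is fair, and it limits the point: a reader might infer that adjusted effects cannot be produced at all, and the text does not show that. But the article is not silent on method. It assigns tests by variable type directly after promising adjustment, and even on the generous reading it does not say which result is the main one.

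A reader might also infer that the unadjusted comparisons are biased. They are not. Allocation is randomised and stratified by gestational age and gender, so balance on those two is already supported by design, within strata. Residual chance imbalance concerns mainly socio-economic score.

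Nor do the missing T0 and sex covariates contradict anything, since section 8.2 promises neither. The Stress Measures section already plans a between-arm comparison of PSS-NICU, and comparing General Movements scores at each time point is not an error. Adding these covariates is an improvement. The power gain, finally, rests on assumed inputs and is small at low correlations. All of this stands.

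**Conclusion.** The point holds in a limited form. Section 8.2 promises adjustment for socio-economic score and gestational age at birth, and the tests it names cannot provide it. The consequence is lost precision and ambiguity about the main result, not bias. Under the assumptions above the gain from adjusting runs from about 2 percentage points of power (r = 0.2) to about 18 (r = 0.6), and the upper end is plausible mainly for General Movements and PSS-NICU. The mismatch itself depends on none of these assumptions. Severity is should-fix: every secondary outcome is affected, the primary outcome is not.

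**What to change.** Rewrite the analysis paragraph of section 8.2 so that a covariate-adjusted model is the main secondary analysis:

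- **Scores:** linear regression or ANCOVA, or proportional-odds regression where scores are skewed or ordinal. Include arm, gestational age at birth as a continuous covariate (as promised), sex (a stratification factor), socio-economic score and, for General Movements and PSS-NICU, the T0 value.
- **Binary outcomes:** logistic or exact regression for any that are compared between arms. There may be few, because section 5.2.1 uses the neurological and audiological results as grounds for exclusion from analysis.
- **Twins:** standard errors that allow for clustering by family, since twins are randomised together.
- **PSS-NICU:** report the between-arm difference at discharge, adjusted for T0.
- **Named tests:** keep Wilcoxon-Mann-Whitney and chi-squared or Fisher's exact as unadjusted sensitivity analyses, labelled as such.

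The bare minimum would be to delete the adjustment sentence. That removes the mismatch but gives up an adjustment the authors say they want.

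The cost is one paragraph. Gestational age, sex, socio-economic score and the two T0 scores are already collected. The downside is modest modelling assumptions, which the unadjusted sensitivity analyses help to check. The wording should be settled before outcomes are compared by arm, so that the choice of main result cannot depend on the data.
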